## Abstract

**Rationale:** Remote ischemic perconditioning during cerebral ischemia (RIPerC) refers to the application of brief episodes of transient limb ischemia commonly to a limb, it represents a new safe, simple and low-cost paradigm in neuroprotection.

**Aim and/or Hypothesis:** To evaluate the effects of RIPerC on acute ischemic stroke (AIS) patients, applied in the ambulance, to improve functional outcomes compared with standard of care.

**Sample Size Estimates:** A sample size of 286 patients in each arm achieves 80% power to detect treatment differences of 14% in the outcome, using a two-sided binomial test at significance level of 0.05, assuming that 40% of the control patients will experience good outcome and an initial misdiagnosis rate of 29%.

**Methods and Design:** We aim to conduct a multicentre study of pre-hospital RIPerC application in AIS patients. A total of 572 adult patients diagnosed of suspected clinical stroke within 8 h of symptom onset and clinical deficit >0 according to prehospital rapid arterial occlusion evaluation (RACE) scale score will be randomized, in blocks of size 4, to RIPerC or sham. Patients will be stratified by RACE score scale. RIPerC will be started in the ambulance before hospital admission and continued in the hospital if necessary. It will consist of five cycles of electronic tourniquet inflation and deflation (5 min each). The cuff pressure for RIPerC will be 200 mmHg during inflation. Sham will only simulate vibration of the device.

**Study Outcome(s):** The primary outcome will be the difference in the proportion of patients with good outcomes as defined by a mRS score of 2 or less at 90 days. Secondary outcomes to be monitored will include early neurological improvement rate, treatment related serious adverse event rates, size of the infarct volume, symptomatic intracranial hemorrhage, metabolomic and lipidomic response to RIPerC and Neuropsychological evaluation at 90 days.

**Discussion:** Neuroprotective therapies could not only increase the benefits of available reperfusion therapies among AIS patients but also provide an option for patients who are not candidates for these treatments. REMOTE-CAT will investigate the clinical benefit of RIC as a new neuroprotective strategy in AIS.

**Clinical Trial Registration:**
www.ClinicalTrials.gov, identifier: NCT03375762.

## Introduction and Rationale

Stroke is one of the leading causes of death worldwide and the main cause of disability (1). Currently, the only therapies for acute ischemic stroke (AIS) patients are the administration of rt-PA (2) and/or endovascular treatment (3). Unfortunately, many patients cannot benefit from these therapies due to their contraindications or evolution time. Neuroprotective therapies could not only increase the benefits of available reperfusion therapies but also provide an option for patients who are not candidates for these treatments (4). However, most neuroprotection trials have so far failed to demonstrate their efficacy in AIS patients, despite promising results in animal studies (4). Remote ischemic perconditioning (RIPerC) represents a new paradigm in neuroprotection (5). It potential upregulates endogenous defense systems to achieve ischemic tolerance in brain ischemia (6). It consists of brief episodes of transient limb ischemia. According to studies in coronary ischemia, RIPerC during the ischemic event is safe, feasible, and related to a decrease in myocardial injury (7). However, there is limited data about the clinical utility of RIPerC in AIS patients. Only four randomized clinical trials (RCTs) have been completed and published (8–11). All of them demonstrated that RIC is safe and feasible in AIS. One has been conducted to test RIPerC in a prehospital setting in AIS patients and as an adjunct treatment with intravenous alteplase (11). Two other small-size studies were only designed to evaluate the safety and feasibility of RIC in AIS patients recruited within 24 h of onset of symptoms (8) and in alteplase treated patients (9). The last and the largest study included 188 patients with confirmed carotid ischemic stroke within 6 h of symptoms onset (10). None of them demonstrated a significant clinical effect or a significant effect on brain infarction volume growth.

We aim to conduct a multicentre study of pre-hospital RIPerC in AIS patients applied within 8 h of stroke onset. Our hypothesis is that RIPerC would be safe and would induce endogenous neuroprotective phenomena associated with good outcomes in AIS patients treated with revascularization therapies or not.

## Methods

### Design

REMOTE-CAT is a prospective randomized controlled multicentre clinical trial that follows CONSORT statement (12). The study will be performed in accordance with the standards of good clinical practice (International committee on Harmonization of E6 Guideline for Good Clinical Practice) and the latest revision of the Declaration of Helsinki. The study has been approved by the Ethics Committee on Clinical Research of the Hospital Universitari Arnau de Vilanova of Lleida (approval code 1744). All patients will provide written informed consent. The protocol is registered in ClinicalTrials.gov identifier is NCT03375762.

### Patient Population

Inclusion and exclusion criteria are detailed in Table 1. Summarizing, REMOTE-CAT focuses on patients with suspected acute stroke identified in the pre-hospital setting by emergency medical services (EMS). The EMS is a public company responsible for urgent prehospital care including Code Stroke (CS) patients. We will include consecutive adult subjects (age ≥18 years old) with CS activation will be included. CS activation criteria include neurologic impairment suggestive of acute stroke according to FAST criteria (13), time from symptom onset of <8 h and previous functional independence (modified Rankin Scale, mRS ≤ 2). Patients should have at least motor impairment (Figure 1). Baseline assessments and study procedures are reported in Table 2.

**Table 1 T1:** Inclusion and exclusion criteria.

**Inclusion criteria**
• Age above 18 years old • Suspected clinical stroke within 8 h of onset of neurological symptoms • Stroke code (SC) activation • Independent in daily living before the acute onset of symptoms (mRs ≤ 2) • RACE score>0 and RACE motor score>0 • Written informed consent (patient or legal representative)
**Exclusion criteria**
• Unknown onset of symptoms • Coma (GCS <8) • Malignancy or significant comorbidity thought to limit life expectancy to <6 months • Pregnancy • Participation in other clinical trial related with a research medical product/device

*RACE, The rapid arterial occlusion evaluation scale; mRs, Modified Rankin scale; GCS, Glasgow Coma Scale*.

**Figure 1 F1:**
[figure not shown]
Graphical representation of REMOTE-CAT clinical trial procedures. After Stroke Code activation in the ambulance, remote ischemic perconditioning (RIPerC) is applied by an automatic device during transportion to the nearest Stroke care center. Usual medical care will be performed in the stroke center.

**Table 2 T2:** Study procedures for eligible patients with AIS.

**Time points**	**Prehospital**	**Admission**	**24 h**	**3 days**	**5 days**	**3 months**
Enrollment						
Eligibility screen	✓					
Patient/family information	✓	✓				
Acute waiver of consent	✓					
Randomization	✓					
RACE scale	✓					
Blood pressure	✓	✓^‡^				
Informed consent		✓				
AIS confirmation		✓^*^			✓^*^	
Demographics and medical history		✓				
Reperfusion therapies		✓				
Intervention						
RIC/Sham application	✓					
Complications related to RIC		✓	✓		✓	✓
Assessment						
NIHSS		✓	✓		✓	✓
Modified Rankin scale		✓			✓	✓
Neuroimaging		✓	✓^#^			
MRI				✓		
Blood biomarkers		✓		✓	✓	
Stroke etiology					✓	
Quality of life						✓
Neuropsychological evaluation						✓
Safety measurement						
Intrahospital complications					✓	✓
SICH			✓		✓	

RACE, rapid arterial occlusion evaluation; AIS, acute ischemic stroke; RIC, remote ischemic conditioning; MRI, magnetic resonance imaging; NIHSS, National Institutes of Health Stroke Scale.

‡ Blood pressure will be reported at the end of RIC/Sham application and 1 h after.

* Patients with intracranial hemorrhage will complete the 90 days follow-up. Patients without evidence of brain ischemia will be followed until discharge and through registries.

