### Primary Outcome

The primary outcome will be the difference in the proportion of patients with good outcomes as defined by a mRS score of 2 or less at 90 days.

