### Statistical Analyses

Included patients will be described with respect to demographic and clinical characteristics, according to the study arm. Continuous variables will be summarized using means and standard deviations for normally distributed data; or median and 25–75% percentiles for non-normally distributed data. Normal distribution will be assessed by means of the Shapiro–Wilks test, rejecting normality when *p* <0.05. Categorical data will be summarized using counts and percentages. Comparisons will be performed by means of the Pearson's chi-squared test for categorical variables; the *t*-test for normally distributed data; and the Mann–Whitney *U*-test for non-normally distributed data.

Primary analysis will be performed by means of the binomial test. If the study groups are unbalanced, the primary outcome will be compared using a logistic regression model that will include the variables exhibiting baseline differences as covariates.

Secondary outcomes will be compared using the most appropriate test according to the distribution of the data. As with the primary analysis, secondary outcomes and safety outcome analyses will be conducted using multivariable generalized linear models with suitable links.

The analysis will be performed on the intention-to-treat set and will be repeated on the per-protocol set as a sensitivity analysis.

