### Handling Missing Data

If there are missing data, they will be reported for each variable and missingness mechanism will be explored. Missing values could depend on other observed data. We will consider these missing values as missing at random (MAR). If there is no correlation between the missing values and other observed data (i.e., the Little's test is not statistically significant, *p* > 0.05) missing values will be considered missing completely at random (MCAR) (20). If missing values are MAR, a series of multiple imputations by chained equations will be performed and the Rubin's rules will be used to combine variable estimates and standard errors (21). If missing values are MCAR, complete case analysis will be performed.

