## Discussion

RIPerC emerges as an interesting neuroprotective strategy (5). Our study improves the previous limited experience in humans (8, 11). It includes all AIS with symptom onset within 8 h and not only intravenous alteplase treated patients (11). According to the animal model, it is effective when applied both alone and in combination with revascularization therapies (22, 23). Although few studies have been published about the effect of RIC in AIS, some important issues have been learned (8–11). As in Hougaard's trial (11) and in most of the trials involving patients with myocardial infarction (7, 24) it is applied it in the ambulance, as soon as possible, in order to induce the maximum effect. This action seems to be safe although the definitive diagnosis will not be established until the arrival at the hospital. To date, no serious adverse effects have been reported in RIC studies (5, 7–11, 25). The recent RCT published by Pico et al. failed to demonstrate an effect of RIC in the final infarction size in AIS. One explanation of their neutral results was that the treatment with RIC was performed too late during or after the receipt of reperfusion therapies (10). In addition, we will increase the number of cycles to five. Most RIC trials use the four-cycle protocol (7, 11) due to tradition. The ischemic conditioning phenomena was first demonstrated using this protocol in an animal model of myocardial infarction (26). Recent studies in animal models address the need to increase the number of cycles in order to optimize the efficacy of RIPerC (27). Some other recent successes in remote ischemic preconditioning (28) and chronic postconditioning (29) in AIS patients have used the 5-cycle protocol. Increasing the duration of the cycle to 10 min does not offer any further protection (27). Although the quantity of muscle mass affects the efficacy of the intervention, we decided to perform the RIPerC on an upper arm rather than on a leg for safety reasons as up to one in four AIS patients have silent peripheral arterial disease defined by a low ankle-brachial index (30). One of the main shortcomings of the previously mentioned Hougaard's trial (11) was that fewer than one out of three patients complete the four cycles of limb ischemia. We will therefore use an automatic device. To avoid misdiagnosis only subjects with RACE score of >0 and RACE motor items >0 will be included. Finally, according to the stroke treatment academic industry roundtable (STAIR) recommendations a clinical endpoint would clearly evaluate the utility of applying RIPerC in AIS patients.

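### A 90-day mRS is not assured for randomised patients found to have no brain ischaemia (about 14% on the plan's own figures), although the primary analysis is intention-to-treat

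*Protocol article*

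**What the plan says.** All references are to the protocol article.

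- **Randomisation.** Patients with suspected stroke are randomised in the ambulance. The Discussion accepts that "the definitive diagnosis will not be established until the arrival at the hospital".
- **Primary Outcome.** It is "the difference in the proportion of patients with good outcomes as defined by a mRS score of 2 or less at 90 days".
- **Statistical Analyses.** "The analysis will be performed on the intention-to-treat set", with a per-protocol repeat as sensitivity analysis. No exclusion of misdiagnosed patients is stated.
- **Table 2, footnote marked \*.** "Patients with intracranial hemorrhage will complete the 90 days follow-up". The next sentence reads: "Patients without evidence of brain ischemia will be followed until discharge and through registries". The footnote is attached to the row for confirmation of ischaemic stroke, which is ticked at admission and again at 5 days. The table is titled "Study procedures for eligible patients with AIS".
- **Sample Size Estimates.** A misdiagnosis rate of 29% is allowed for: 15% haemorrhage and 14% mimics.
- **Handling Missing Data.** If values are judged missing at random, "a series of multiple imputations by chained equations will be performed". If Little's test is not significant, complete cases are used.

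**The concern.** The footnote sets two follow-up rules according to a diagnosis made after randomisation. Haemorrhage patients are expressly kept to 90 days. The contrast implies that patients in whom no ischaemia is found have no scheduled 90-day visit. They still belong to the intention-to-treat set, so the primary analysis needs their 90-day mRS.

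This is a data-collection rule, and an analysis plan cannot recover an mRS that was never recorded. Nor do the missing-data rules fit the case. The outcome would be absent because of the diagnosis, and nobody with that diagnosis might have it observed. Complete-case analysis would then remove the whole group. Imputation would have to carry over the relation between early status and day 90 from stroke and haemorrhage patients.

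The timing adds a second issue. The second confirmation point, day 5, falls after the intervention and after the day-3 MRI, so the diagnosis that governs follow-up could itself be affected by treatment.

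**Working it through.** **1. The plan's own sample size.** Inputs from Sample Size Estimates: 40% v 54%, two-sided 0.05, 80% power, 29% misdiagnosed, factor 1.02.

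Pooled normal approximation without continuity correction:

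n = [1.96·√(2·0.47·0.53) + 0.8416·√(0.40·0.60 + 0.54·0.46)]² / 0.14² = 199 per arm.

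199/0.71 = 280.3 (stated 280). 280 × 1.02 = 285.6, so 286 per arm and 572 in all. The figure is reproduced. Dividing by 0.71 treats all 29% misdiagnosed patients as contributing nothing, which fits an analysis of confirmed ischaemic stroke rather than intention to treat.

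**2. Patients affected.** 0.14 × 572 = 80, about 40 per arm. This takes the planning figure for mimics as the share in whom no ischaemia is found.

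**3. Intention-to-treat difference if everyone is observed.** Assume 14 points in the 71% with ischaemic stroke and no effect in the other 29%: 0.71 × 14 = 9.9 points.

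**4. Difference if mimics are dropped, or imputed with nothing to separate them.** 0.71 × 14 / 0.86 = 11.6 points.

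The arm rates shift too. Assume good outcome in 80–90% of mimics and 20–30% of haemorrhages:

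- Smallest shift (80%, 30%, RIPerC arm): 0.71·0.54 + 0.14·0.80 + 0.15·0.30 = 54.0% with everyone, against (0.71·0.54 + 0.15·0.30)/0.86 = 49.8% without mimics, 4.2 points too low.
- Largest shift (90%, 20%, control arm): 0.71·0.40 + 0.14·0.90 + 0.15·0.20 = 44.0%, against (0.71·0.40 + 0.15·0.20)/0.86 = 36.5%, 7.5 points too low.

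**5. Power under full intention to treat.** With 9.9 points and 280 per arm, power is about 65%, and about 396 per arm would be needed for 80% before the interim inflation. This hardly moves for assumed good-outcome rates of 70–100% in mimics and 20–40% in haemorrhage.

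**6. If the primary set is confirmed ischaemic stroke instead.** Suppose a share *a* of RIPerC stroke patients end with no visible ischaemia and a good outcome, and are excluded, with no such loss in control. The RIPerC rate becomes (0.54 − *a*)/(1 − *a*). Power is at 286 × 0.71 = 203 per arm, where it is 81% without loss. The documents give no value for *a*, so these are assumptions:

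| *a* | Difference (points) | Power |
|---|---|---|
| 1% | 13.5 | 78% |
| 2% | 13.1 | 75% |
| 5% | 11.6 | 65% |
| 8% | 10.0 | 53% |

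With loss in both arms the result depends on the imbalance. At 5% v 2%, 0.49/0.95 − 0.38/0.98 = 12.8 points. At an equal 5%, 0.49/0.95 − 0.35/0.95 = 14.7 points, so equal loss does not bias towards no effect.

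Steps 4 and 6 belong to different analysis sets and point in opposite directions. They must not be added.

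**The case against.** **Registries may supply the outcome.** A reader might infer that the mRS is missing by design. The footnote does not go that far, because follow-up continues through registries and a condensed article may leave their names to the full protocol. This stands: the supported wording is that a 90-day mRS is not assured.

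**The analysis can be run.** A reader might also infer that the intention-to-treat analysis is impossible as written. It is not, since Handling Missing Data gives a rule for every missing value. What remains open is whether that rule is credible for a group with possibly no observed day-90 value.

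**Imputation may do better than step 4.** Table 2 schedules NIHSS and mRS at admission and day 5, and chained equations can use what is collected before discharge. This stands, and makes 11.6 points an upper-end case. The step from early status to day 90 in mimics would still be unobserved.

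**The intended set may be confirmed ischaemic stroke.** The title of Table 2 and the division by 0.71 suggest so. Then mimics are neither missing nor imputed, and step 4 falls away. But Statistical Analyses names the intention-to-treat set without exclusion, and selection on a diagnosis confirmed as late as day 5 would then enter the primary set directly. The problem changes form rather than going away.

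**Averted strokes are hypothetical.** This stands as to size. The article gives no criterion for absence of ischaemia. It does not say that a negative MRI or rapid recovery reclassifies a patient, and it gives no rate.

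**Conclusion.** The point holds in this form: the Table 2 footnote does not assure the primary outcome for a group that is defined after randomisation and that the stated analysis set includes. On the protocol's planning figure the group is about 14% of patients, or about 80 of 572; the true share may differ.

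Under full intention to treat, the illustrative cost is an expected difference of 11.6 points in place of 9.9. It rests on a 14-point effect in ischaemic stroke, none in the other 29%, equal mimic shares in both arms, and no early information that separates mimics. On the same terms, with no effect in any group, step 4 gives zero. The distortion is therefore in the size of the effect and the population it describes, and does not by itself create a difference.

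Under an analysis of confirmed ischaemic stroke, the risk is a bias towards no effect if treatment moves patients out of the set. The documents make this possible but do not show it, and they support no particular size.

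The protocol does not say consistently which of the two sets is meant: Statistical Analyses points to one and Sample Size Estimates to the other.

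**What to change.** 1. Collect the 90-day mRS for every randomised patient whatever the final diagnosis, within the ±7 days already used for NIHSS under Secondary Outcomes. Telephone is enough. Change the Table 2 footnote accordingly, or name a registry that supplies a 90-day mRS.
2. Have the final diagnosis classified blind to arm, by a stated criterion.
3. Reconcile the intention-to-treat set in Statistical Analyses with the 29% allowance in Sample Size Estimates, and state which set is primary.

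**Cost.** About 80 further calls and one footnote. The larger consequence is for power. If full intention to treat is kept, the stated 80% must be restated: about 65% at 280 per arm if there is no effect outside ischaemic stroke. Recruitment was under way (76 patients by 1 August 2020), and a 90-day mRS not taken at the time may not be recoverable, so the change is worth making early.

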# *Patients treated with intravenous rtPA and/or EVT will undergo neuroimaging at 24 h*.

### Randomization

First, patients will be stratified using the rapid arterial occlusion evaluation (RACE) scale score (14) and then, they will be randomly allocated in blocks of size four, to either receive remote ischemic conditioning (RIPerC group) or sham in the ambulance. An on-call physician not involved in the study will perform the randomization using a computer program located in a web server.

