### Intervention

RIPerC will consist of automatically delivered five cycles of electronic tourniquet inflation to the upper non-paretic limb, each lasting 5 min and separated by 5 min of cuff deflation. The cuff will be inflated to 200 mmHg and it will be applied to the opposite arm to the one experiencing motor and/or sensory deficit in order to reduce the risk of phlebitis and to maintain the somatosensory stimuli. RIPerC will be initiated by the ambulance staff during transportation and it will be finished for all patients in the ambulance or during Hospital admission. All patients in both groups will be treated according to conventional care procedures following international guidelines. Thus, mechanical thrombectomy and intravenous fibrinolysis will be allowed. Revascularization therapies will not be delayed due to the study. The non-interventionist group will use a sham device. It will simulate vibration of the device but no inflation will be performed. Discomfort and complications related to RIPerC will be recorded.

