### Sample Size Estimates

A sample size of 280 subjects in each arm achieves 80% power to detect treatment differences of 14% between the intervention and the control groups, using a two-sided binomial test at significance level of 0.05, assuming that 40% of the control patients will experience good outcome defined by a mRS score of 2 or less at 90 days, and allowing a misdiagnosis rate of 29% (15% of haemorrhagic strokes and 14% of mimic stroke conditions). Two extra interim analyses will be performed at 33 and 67% of recruitment on the primary outcome. Early stopping is planned if large differences between the study groups are observed in order to reduce study participants' exposure to the inferior study arm and saving time and resources. Since repeated significance testing on accumulating data will be performed, adjustment of the usual hypothesis testing procedure to maintain the overall significance level of 0.05 will be done by using the flexible type I error spending function (18, 19). Due to the interim analyses, the sample size must be increased by an inflation factor of 1.02, resulting in 572 patients (286 per group).

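### A single disclosed block size of four lets a fully informed observer know up to a third of allocations in advance; randomly varied sizes would remove most of that certainty at small cost

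*Protocol article*

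**What the plan says.** The Randomization section of the protocol article states that "patients will be stratified using the rapid arterial occlusion evaluation (RACE) scale score" and that "they will be randomly allocated in blocks of size four". The abstract gives the same single size: patients "will be randomized, in blocks of size 4, to RIPerC or sham". RACE score is the only stratification factor named. The article does not say whether each site has its own list.

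On who allocates, the same section says: "An on-call physician not involved in the study will perform the randomization using a computer program located in a web server".

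On what can be seen afterwards, the Intervention section says of the active arm "The cuff will be inflated to 200 mmHg" and of the sham "It will simulate vibration of the device but no inflation will be performed". It also says that "RIPerC will be initiated by the ambulance staff during transportation".

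The section on the current status of the trial gives 76 patients recruited at 1 August 2020, a start in one hospital in August 2019, and estimated completion in August 2022. Sample Size Estimates sets the total at 572, with 286 per group.

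**The concern.** With equal arms and a block of four, each block holds two RIPerC and two sham allocations. Once both places of one arm are used, the rest of the block is fixed. Anyone who knows the block size, can recognise past arms and can follow the sequence will sometimes know the next arm before the next patient is entered.

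Past arms are probably recognisable to people near the device, because one arm has repeated inflation and the other has none. Table 2 places eligibility screening, RACE scoring and randomization all before hospital arrival. Entry rests on quick judgements there: suspected stroke, time since onset, and presence of a motor deficit. If the next arm were known, those judgements could be swayed, and the arms could differ in prognosis before treatment starts. The planned logistic model adjusts for variables that show baseline differences, so it reaches measured factors only.

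**Working it through.** **Inputs.** Block size 4 and two arms (Randomization; abstract). Equal allocation, 286 per group (Sample Size Estimates). Recruited 76 of 572 at 1 August 2020 (current status). The article states no figure for predictability, so there is none to reproduce.

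**The plan's sample size.** A 40% against 54% comparison at 80% power and two-sided 0.05 needs 199 per arm. Allowing for 29% misdiagnosis gives 199/0.71 = 280.3, against the stated 280. Then 280 × 1.02 = 285.6, or 286 per arm and 572 in total. Block size does not enter this calculation, so changing it leaves 572 as it is.

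**Certain allocations, fixed block of four, full view.** There are 6 equally likely orders of two A and two B. Two of them (AABB, BBAA) fix the last two places; the other four fix only the last.

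(2 × 2 + 4 × 1) / (6 × 4) = 8/24 = 33.3%

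**Best guess, same observer.** The chance of a correct guess at places 1 to 4 is 1/2, 2/3, 2/3 and 1. At place 3 the allocation is certain one time in three and even otherwise: 1/3 + (2/3)(1/2) = 2/3.

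(1/2 + 2/3 + 2/3 + 1) / 4 = 17/24 = 70.8%, against 50% for simple randomization

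Neither result depends on the number of RACE strata, which is not given.

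**Partial view.** Assume the observer sees each earlier allocation independently with probability f and still knows the block boundaries. An allocation is certain only if both places of one arm have gone and both were seen. The share is [(1/3)f² + f²]/4 = f²/3.

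| Share seen, f | Certain allocations |
|---|---|
| 100% | 33.3% |
| 80% | 21.3% |
| 50% | 8.3% |
| 25% | 2.1% |

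**Randomly varied blocks, full view.** This was simulated over 400,000 allocations, with sizes equally likely and an observer who knows the possible sizes and the whole history of the stratum.

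| Block sizes | Certain | Best guess correct | Largest open-block imbalance |
|---|---|---|---|
| 4 fixed | 33.3% | 70.8% | 2 |
| 4, 6 | 5.4% | 69.3% | 3 |
| 4, 6, 8 | 2.2% | 68.1% | 4 |

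The last column is half the largest block.

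**Patients a change could reach.** 572 − 76 = 496, which is 496/572 = 87% at 1 August 2020.

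**The case against.** The strongest reply is that no role in the article both decides entry and sees the sequence. Allocation goes through a web server, run by a physician outside the study. An ambulance crew sees its own patients and not a whole RACE stratum. The trial is multicentre and names only RACE as a factor, so one list may run across sites and be harder to follow. Patients are also to be enrolled consecutively, which narrows the room for selection. All of this stands as mitigation. It does not remove the risk: the on-call physician probably sees each result, although the article does not say so, and recruitment began in one hospital, where following a stratum is easiest.

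It can also be said that the remedy does little for guessing. That is correct: 70.8% falls only to about 68%, and selective entry could act on a good guess. The gain is the removal of certainty.

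The slow pace so far, 76 in about a year, is weak support for the concern. Finishing by August 2022 would need about 496/24 = 21 patients a month, against about 76/12 = 6.

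A reader might infer that anyone involved can foresee a third of allocations, or that entry has already been selective. The article supports neither. One third requires sight of every earlier allocation in a stratum and of the block boundaries, and nothing in the text points to actual subversion. Recognition of the arm is itself an inference from inflation against no inflation; no test of blinding is reported.

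**Conclusion.** The point holds as a good-practice improvement. It is not an error or a contradiction: fixed blocks of four with central web allocation are an acceptable choice. The weakness is that one size is stated openly, in a trial still recruiting at the reported date, where past arms are probably recognisable.

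Its size is at most 33% of allocations certain and 71% guessed correctly. The certain share drops with the square of the proportion of earlier allocations seen. The result assumes equal allocation within each block and recognisable arms, and the upper bound also assumes complete sight of a stratum. The figure of 496 patients remaining belongs to 1 August 2020; the article gives no count at the time of publication.

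It would also be too strong to call the change free, since it means altering a live system and accepting slightly larger possible imbalance.

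**What to change.** For all patients still to be randomised, have the web program draw block sizes at random, for example from 4, 6 and 8, within each RACE stratum. Decide in advance how blocks open at the changeover are handled. Keep the new sizes out of any document that sites and on-call physicians can read, and describe them publicly only after recruitment ends.

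The cost is a new list in the live allocation system and a possible imbalance of up to 4 rather than 2 patients per stratum within an open block, including at an interim look. The sample size, intervention, outcome and analysis do not change.
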